During match play, the optimal placement of a ball to beat the opposing goalkeeper is at the top and bottom corners of the goal and the points associated with each scoring zone will reflect this (Fig. 2). Furthermore, a coach would normally encourage the players to shoot across the goalkeeper towards the open space of the goal [12]. To replicate this within the LSST, the players will be told that they can only score points if the ball strikes the open side of the goal, i.e., the half not covered by the mannequin goalkeeper.

Both left and right feet will be used during the LSST. The trial orders will be devised so that players have five shots for each foot per trial. The final score will be the mean of the total cumulative points accrued from all the shots on target. Those shots that were attempted from outside the shooting zone, took more than 8.5 seconds to complete, and/or were struck at less than 64 km · h^-1^, will be completely disregarded.

The assessments will have the same order for every participant regardless of the interventional arm allocation and will be conducted as follows: (1) LSPT numbers 1; (2) LSST numbers 1; (3) LIST-P; (4) LSPT numbers 2; and (5) LSST number 2 (Fig. 4).

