### Randomization

We will use block-stratified randomization, with random 2 − 4 sized blocks and stratified by gender. A statistician not related to the protocol will generate the randomization list using a web-based method (http://www.randomizer.org) that will randomize the order of the interventions assigned. We will then have sequentially numbered, sealed, opaque envelopes with the allocations inside, in order to maintain allocation concealment throughout the randomization process. After the patient is consented and enrolled in the trial, an un-blinded endocrinologist (also in charge of the educational sessions) will open the assigned envelope, allocate the subject to the group presented and coordinate with the pharmacy and nutritional department for the preparation of the insulin and dietary modifications needed with respect to the interventional arm assigned.

As mentioned before, the main objective that guides this exercise protocol is not to demonstrate differences in the response of subjects with T1D to different exercise modalities, such as continuous versus intermittent exercise. On the contrary, we want to evaluate the impact, in terms of safety and performance, of a protocol that sets forth insulin dosage along with carbohydrate intake diet modifications, compared with usual-care recommendations stated by guidelines for standard of care. This being said, it is worth adding that other trials [2, 10, 11] have evaluated the response of subjects to the 4-step method, so we would be increasing knowledge of this particular intervention.

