### Statistical methods

In order to evaluate glucose control, we will also compare the two groups, using either Student’s paired *t* test or the Wilcoxon-Mann-Whitney test, in terms of CGM parameters that include: 24-h mean glucose levels, SD of 24-h glucose levels, area under the curve for 24-h glucose, mean amplitude of glycemic excursions, number of episodes of hypoglycemia (<60 mg · dL^-1^), time in hypoglycemia (<60 mg · dL^-1^) during a 24-h period, time in hyperglycemia (>180 mg · dL^-1^) during a 24-h period, and range of postprandial glucose increase. The range of glucose increase (from pre-meal to post-prandial peak levels) after breakfast, lunch, and dinner, will also be compared between the interventional groups, using either repeated measures analysis of variance (ANOVA) or the Kruskal-Wallis test, depending on the normality of the data distribution.

We will assess for data from the LIST-P, LSPT, and LSST, and the Stroop, DVT, DBT, and RVIP test scores obtained for each assessment session, for normality of distribution using histogram analysis, the Shapiro-Wilk test and the Kolmogorov-Smirnov test. We will use a logarithmic transformation for the correction of non-normal data and will subsequently test for the differences between groups using Student’s paired *t* test. In order to assess if the order of the intervention modified the performance of individual participants, we will calculate the difference of the scores obtained between the two types of interventions (real intervention minus sham 4-step method) and then we will define an intervention indicator variable that will take the value of 1 if the subject started with the real 4-step method, and 0 if the subject started with the sham 4-step method. We will then fit a linear regression model with the difference calculated as the response variable and the intervention indicator along with other relevant covariates (age, gender, BMI) as the independent variables. Moreover we will test for time effect over the performance of the participants in a time-varying regression model. Additionally, Pearson correlation coefficients will be calculated between each of the scores and the pre-exercise blood glucose level, searching for linear correlation between blood glucose values and the LIST-P, LSPT, LSST, and Stroop test scores.

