In the event that the data do not follow the normal distribution even after the log-transformation, we will conduct non-parametric analyses using the Wilcoxon-Mann-Whitney test and calculate Spearman correlation coefficients for the comparison between the two groups of the performance scores in soccer and cognitive tests, and for the linear correlation analysis, respectively. A *p* value <0.05 will be considered significant for the comparison of the scores.

Additionally, we will conduct exploratory analyses by modeling the performance scores in soccer evaluations adjusted by age, years since T1D diagnosis, HbA1c level, weekly physical activity hours and Stroop test scores using linear multiple regression. A *p* value <0.10 will be considered significant to introduce a variable into the multivariate regression model. The number of hypoglycemic events and the percentage of other adverse effects listed previously will also be compared among groups using Student’s *t* test and the Fisher exact test, respectively. All of the statistical analysis will be done using Stata software (StataCorp LP® 13.1).

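### The exploratory regression of soccer scores omits gender, the stratification factor, so a gender effect can be credited to a listed covariate if gender is related to both

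*Protocol article*

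**What the plan says.** Three places in the protocol article bear on this.

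- **Statistical methods, exploratory model.** A multiple linear regression is planned for "modeling the performance scores in soccer evaluations adjusted by age, years since T1D diagnosis, HbA1c level, weekly physical activity hours and Stroop test scores". A p "value <0.10 will be considered significant to introduce a variable into the multivariate regression model". No gender, regimen, period or participant term is named. The text does not say whether one score per person or the scores of both sessions are modelled.
- **Randomization.** "We will use block-stratified randomization, with random 2 − 4 sized blocks and stratified by gender".
- **Statistical methods, order regression.** Here "we will calculate the difference of the scores obtained between the two types of interventions (real intervention minus sham 4-step method"), and that difference is regressed on "the intervention indicator along with other relevant covariates (age, gender, BMI) as the independent variables".

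The same section compares soccer scores between regimens by a paired t test and examines order and time in separate models. In the shooting test, shots that "were struck at less than 64 km · h^-1^, will be completely disregarded"; that threshold is the same for all players. In the shuttle test, by contrast, the prescribed pace is set from each participant's own VO2max.

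**The concern.** Gender is adjusted for where it matters less and left out where it matters more. In a real-minus-sham difference, anything constant within a person drops out, including a gender main effect. In a model of the scores, the gender effect stays in the data. If the model has no gender term, that effect goes to whichever listed covariates are related to gender, and the rest goes to the residual.

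A gender effect on at least some scores is plausible from the design, because the shooting test's 64 km/h limit and the passing test's 43 s limit are not scaled by gender.

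What is at stake is the list of apparent predictors of soccer performance. Weekly activity, for example, could be named as a predictor when it only stands in for gender.

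**Working it through.** The plan attaches no figure to this model, so there is none of its own to reproduce. Its sample size supplies the n: 24 before dropout, and 24 × 1.15 = 27.6, rounded up to the target of 28.

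**1. Size of the false coefficient.** Let g be the gender effect on the score, p the share of women, and d the gender gap in activity, with g and d in within-gender SDs. If activity has no true effect and gender is omitted, the expected activity coefficient is

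g · p(1−p)d / [1 + p(1−p)d²].

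- g = 1, d = 0.5, p = 0.25: 0.1875 × 0.5 / (1 + 0.1875 × 0.25) = 0.094 / 1.047 = 0.09.
- g = 2, d = 0.8, p = 0.25: 2 × 0.1875 × 0.8 / (1 + 0.1875 × 0.64) = 0.300 / 1.120 = 0.27.
- g = 0 or d = 0: zero. Both links are needed.

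**2. How often activity enters falsely.** This was simulated by ordinary least squares with one averaged score per person and n = 24. The covariates were age, duration, HbA1c and activity. Stroop was left out, and entry was judged by the p value in the joint model. The values of p, g and d are assumptions, because the protocol gives none of them.

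| Women | Gender effect (SD) | Activity gap (SD) | Entry at p<0.10, gender omitted |
|---|---|---|---|
| 25% | 1 | 0.5 | 12.1% |
| 25% | 1 | 0.8 | 15.7% |
| 25% | 1.5 | 0.8 | 20.4% |
| 25% | 2 | 0.8 | 26.2% |

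With gender included, the rate is 9.6–10.4% in these settings. With 40% women the range without gender is 13–33%.

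Milder assumptions at n = 24 and 25% women give about 10% with no activity gap, about 11% with a 0.2 SD gap even for a 2 SD gender effect, and about 11–12% with a 0.5 SD gender effect at gaps of 0.5–0.8 SD.

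A separate simulation at n = 28 with five covariates, tested at 0.05 with a 50:50 split, agrees in direction. With gender omitted, rejection of a null activity effect is about 5% when gender and activity are uncorrelated. It is 9% and 19% at correlations of 0.3 and 0.5 with a 1 SD gender effect. With gender included it is about 5%.

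**3. Precision.** In the four tabulated settings the mean standard error of HbA1c is 0.247–0.306 without gender and 0.235–0.238 with it. The ratios run from 0.247/0.235 = 1.05 to 0.306/0.238 = 1.29, so it is about 5–29% larger. HbA1c and age themselves enter at 9–11%, the nominal rate, because no gender gap was assumed for them.

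**4. Regimen and period.** With complete pairs, each person contributes one score under each regimen and one in each period. A regimen or period indicator therefore has the same mean in every person and zero covariance with gender, age, HbA1c or activity. Leaving it out cannot move a gender effect onto those covariates.

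**5. If both sessions are pooled without a participant term.** The standard error of a person-level covariate is too small by a factor of about √(1+ρ), where ρ is the within-person correlation. At ρ = 0.5 this is √1.5 = 1.22. Simulated at n = 28, the false-positive rate at the 0.05 level is 9%, 12% and 18% for assumed ρ of 0.3, 0.5 and 0.8. Stroop is measured after each session, so it varies with regimen and period, and without those terms its coefficient can absorb their effects.

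**The case against.** The model is labelled exploratory, and the article condenses a fuller plan that is not shown. The covariate list need not be exhaustive. Regimen, order and time are each analysed elsewhere in the same section. Adjusting a within-person difference for gender does not oblige the authors to adjust a different model for it. The simulated sizes rest on assumed effects and gaps, and the upper end needs a 2 SD gender effect together with a 0.8 SD activity gap. Nor are all soccer measures on a common scale for everyone: the speed limit belongs to the shooting test only, and shuttle pace is individual.

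Most of this stands and keeps the point small. It does not remove it. The article names specific covariates and an entry rule, and applied as written that list never offers gender as a candidate.

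Two stronger readings are tempting and are not supported. A reader might infer that gender differences will be reported as effects of activity, HbA1c or age. That needs gender to be related to both the score and the covariate, and the documents report neither; the calculations show false entry for activity only. A reader might also infer that the missing regimen and period terms cause the gender problem or weaken the regimen comparison. Step 4 shows that they do not cause it, and the regimens are compared separately by a paired test.

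**Conclusion.** The point holds as a conditional, minor one. The exploratory model of soccer scores omits the factor on which the trial stratifies, and in that model a gender effect does not cancel. If gender is related to both the score and activity to the assumed extent, false entry of activity rises from about 10% to roughly 12–26% (n = 24, 25% women). If either link is weak or absent, the rate stays near nominal and what may be lost is precision.

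The absence of regimen, period and participant terms matters only if the scores of both sessions enter the model. The primary hypoglycemia outcome and the paired comparison of regimens are untouched.

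**What to change.** State in the exploratory paragraph of Statistical methods that gender is included in the soccer-score model irrespective of its p value, and that the p<0.10 rule applies to the other covariates. State also which session's scores are modelled. If both are used, include regimen, period and a participant effect, for example as a random intercept in a mixed model.

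The cost is a sentence or two of text and no new data, since gender is already recorded for stratification. Gender takes one degree of freedom: with 24 participants, an intercept and five covariates (one Stroop score), residual degrees of freedom fall from 18 to 17. Using both sessions also means replacing ordinary regression with a mixed model. If very few participants are of one gender, the gender coefficient will be imprecise and should be reported as such.

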### Sample size

We estimated a sample size of 24 participants per group, yielding a total sample size of 48 participants. However, because of the crossover design of this trial we will only need a total of 24 participants, as each of them will participate in both interventional arms. We used the following parameters for the sample size calculation: an alpha value of 0.05, power of 80%, two different intervention groups with a crossover design, and a minimal clinically important difference between the groups compared of 40% in the frequency of hypoglycemic events. Considering also a 15% dropout rate during the clinical trial, we obtained a required sample size of 28 participants for each group.

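### The named fallback tests, and Fisher's test for adverse effects, treat the two arms of this crossover as independent groups; they are conservative and lose power if a person's two results are positively correlated.

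*Protocol article*

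**What the plan says.** Trial design describes a randomized crossover with a three-week washout. Sample size relies on this to halve the number recruited: "we will only need a total of 24 participants, as each of them will participate in both interventional arms".

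Statistical methods then assigns tests as follows.

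- **CGM parameters** (including number of hypoglycemia episodes and time in hypoglycemia): paired t test or Wilcoxon-Mann-Whitney.
- **Meal excursions:** "using either repeated measures analysis of variance (ANOVA) or the Kruskal-Wallis test", depending on normality.
- **Soccer and cognitive scores:** log transformation if non-normal, then a paired t test. If the data are still non-normal, "we will conduct non-parametric analyses using the Wilcoxon-Mann-Whitney test".
- **Safety:** "The number of hypoglycemic events and the percentage of other adverse effects listed previously will also be compared among groups". For the event counts the method is a t test with no mention of pairing; for the percentages it is Fisher's.

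The section also regresses the within-person score difference on treatment order. It names no signed-rank, Friedman, McNemar, conditional or mixed-model analysis. The primary outcome is the percentage of participants with at least one confirmed episode in 24 hours; no test is tied to it by name. Normality is assessed on the scores from each session.

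**The concern.** Mann-Whitney, Kruskal-Wallis and Fisher all assume that the two samples come from different people. Failing a normality check does not make paired data independent, yet the plan moves from a paired to an unpaired test on exactly that trigger. It offers the paired t test with Mann-Whitney, and repeated measures ANOVA with Kruskal-Wallis, as if each pair answered the same question.

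Two things are at stake. First, the design buys precision by using each person as their own control, and an unpaired test gives that up. Second, safety measures are the most exposed: 24-hour episode counts and time below 60 mg/dL are likely to be skewed with many zeros, so the fallback is a probable route. The article counts an equal or smaller number of events as an adequate safety profile. An over-conservative test could therefore leave a real difference in hypoglycemia undetected.

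**Working it through.** **Inputs from the article:** "an alpha value of 0.05, power of 80%, two different intervention groups with a crossover design"; 24 participants, each in both arms; "minimal clinically important difference between the groups compared of 40% in the frequency of hypoglycemic events".

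**Assumptions (not in the article):** two-sided testing; the 40% read as 40 absolute points; control rate (70% versus 30% used); within-person correlation (r or phi), shown as a range.

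**1. The plan's own figure.** With the independent two-proportion formula and a mean rate of 0.5,

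n = [1.96·√(2·0.5·0.5) + 0.842·√(0.7·0.3 + 0.3·0.7)]² / 0.4² = (1.386 + 0.545)² / 0.16 = 23.3, so 24 per group.

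Control rates from 60% to 80% give 23 to 24. The stated 24 is thus reproduced by an independent-group calculation, and is then used as the crossover total.

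**2. Why pairing matters for a continuous outcome.** With unit SD, the mean difference has variance 2(1−r)/n, but an unpaired test assumes 2/n. Its true type I error is roughly P(|Z| > 1.96/√(1−r)):

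- r = 0.3: P(|Z| > 2.34) = 1.9%
- r = 0.5: P(|Z| > 2.77) = 0.6%
- r = 0.7: P(|Z| > 3.58) = 0.03%
- r = −0.3: P(|Z| > 1.72) = 8.6%

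For power at r = 0.5 and a 0.5 SD shift:

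- Paired: 0.5/√(2·0.5/24) = 2.45, so power is about Φ(2.45 − 1.96) = 69%.
- Unpaired: 0.5/√(2/24) = 1.73, so power is about Φ((1.73 − 1.96)/√0.5) = 37%.

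**3. Simulation of the named test against its paired counterpart** (24 pairs, bivariate normal, 0.5 SD shift):

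| r | Mann-Whitney power | Signed-rank power | Mann-Whitney type I error |
|---|---|---|---|
| 0.3 | 36% | 50% | about 2.4% |
| 0.5 | 35% | 64% | 0.6-1% |
| 0.7 | 31% | 85% | 0.1-0.2% |

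Separate runs differ by a point or two. The signed-rank test stays at about 5% under the null.

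**4. Exact enumeration for a paired percentage** (24 pairs, 70% versus 30%). The probability of an event in both periods is p₁p₂ + phi·√[p₁(1−p₁)p₂(1−p₂)]. At phi = 0.3 this is 0.21 + 0.3·0.21 = 0.273, so the discordant probabilities are 0.427 and 0.027. Phi cannot exceed (0.30 − 0.21)/0.21 = 0.43.

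| phi | Fisher | Exact McNemar | Mid-p McNemar |
|---|---|---|---|
| 0 | 75% | 70% | 78% |
| 0.1 | 76% | 75% | 82% |
| 0.2 | 77% | 81% | 87% |
| 0.3 | 79% | 87% | 92% |

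Type I error at 50% versus 50%:

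- phi 0: Fisher 2.9%, exact McNemar 2.4%, mid-p 4.3%.
- phi 0.3: Fisher 0.9%, exact McNemar 2.0%, mid-p 4.0%.

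**The case against.** **Pairing is not ignored throughout.** A paired t test or repeated measures ANOVA is the first choice for CGM data and meal excursions. Scores are log-transformed and given a paired t test before Mann-Whitney is reached, and the order-effect regression uses within-person differences. This stands: the defect lies in the fallbacks and the safety sentence, not in every analysis of non-normal data.

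**Fisher is not assigned to the primary outcome.** A reader might infer that it is, because it is the only test given for any percentage. The text ties it to other adverse effects, and a condensed article may leave the primary test to a fuller document. The stronger reading is not supported. What remains is that Fisher should not be carried over.

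**The t test for event numbers may be meant as paired.** It is unlabelled. That it is unpaired is inferred only from the word paired being used elsewhere in the section.

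**The loss can be made to look larger than it is.** At 60% versus 30% and phi = 0.5, Fisher has 44% power against 73% for exact and 85% for mid-p McNemar. But 0.5 is close to the largest phi those margins allow (about 0.53), and the gap is 30 points rather than 40. At phi = 0 with the same margins, Fisher (47%) beats exact McNemar (42%). Some of Fisher's low type I error is also the discreteness shared by exact tests.

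**Wrong error rates might suggest false positives.** Under the expected positive correlation the error is in the conservative direction. Inflation, to about 8% at r = −0.3, needs a negative correlation.

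**Conclusion.** The plan states tests that do not fit its design. Fisher for adverse-effect percentages, Wilcoxon-Mann-Whitney for CGM parameters and for scores still non-normal after the log, and Kruskal-Wallis for meal excursions are wrong for data in which each person supplies both arms. The t test for event counts is probably in the same position, but needs clarifying.

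The cost depends on a correlation the article does not give. For continuous outcomes it is substantial at moderate correlation: about 14, 29 and 54 points of power at r = 0.3, 0.5 and 0.7 (50−36, 64−35, 85−31). For a percentage at the 40-point difference it is smaller: 3 to 13 points against mid-p McNemar over phi 0 to 0.3 (78−75, 92−79), and exact McNemar gains only above about phi 0.1. Near zero correlation almost nothing is lost. These figures assume 24 complete pairs, two-sided 0.05, normal data for the continuous case, and 70% versus 30% for the binary case.

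**What to change.** In Statistical methods:

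- Replace Wilcoxon-Mann-Whitney by the Wilcoxon signed-rank test.
- Replace Kruskal-Wallis by a mixed model or Friedman. With only two interventions Friedman reduces to a sign test, so the mixed model is the better choice.
- Replace Fisher by McNemar, preferably mid-p, or by a period-adjusted form such as Mainland-Gart or conditional logistic regression with a period term. Name the same method for the primary percentage, with a paired risk difference and 95% confidence interval.
- Analyse the number of hypoglycemic events by a paired or mixed count model, and say so explicitly.
- Check normality on within-person differences (or model residuals), not on the raw scores of each session.

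The cost is a rewording of one section. Recruitment is listed as pending, and no extra participants, visits or data are needed.

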### Ethical considerations

The principal investigator and the research assistant for the trial will be responsible for enrolling and contacting participants and conducting the informed consent process. All participants will be assigned an individual code and any personal health information (PHI) that may identify the participants will be protected, and only the research team will have access to it. Any relevant changes in the study protocol and/or the informed consent will be submitted to the independent review board either as protocol deviation report or as protocol amendments. The protocol will be registered in www.isrctn.com before starting with the trial.

